## Abstract

**Background:**

Dental caries incidence in adults is similar to that in children and adolescents, but few caries preventive agents have been evaluated for effectiveness in adults populations. In addition, dentists direct fewer preventive services to their adult patients. Xylitol, an over-the-counter sweetener, has shown some potential as a caries preventive agent, but the evidence for its effectiveness is not yet conclusive and is based largely on studies in child populations.

**Methods/Design:**

X-ACT is a three-year, multi-center, placebo controlled, double-blind, randomized clinical trial that tests the effects of daily use of xylitol lozenges versus placebo lozenges on the prevention of adult caries. The trial has randomized 691 participants (ages 21-80) to the two arms. The primary outcome is the increment of cavitated lesions.

**Discussion:**

This trial should help resolve the overall issue of the effectiveness of xylitol in preventing caries by contributing evidence with a low risk of bias. Just as importantly, the trial will provide much-needed information about the effectiveness of a promising caries prevention agent in adults. An effective xylitol-based caries prevention intervention would represent an easily disseminated method to extend caries prevention to individuals not receiving caries preventive treatment in the dental office.

**Trial Registration:**

ClinicalTrials.Gov NCT00393055

## Background

Dental caries is a significant problem for adults. Despite a widely held perception that caries is a disease of childhood, it has become clear that the incidence of new lesions in adults is approximately the same as the incidence in adolescents [1]. Dentistry has been slow to recognize and address this problem. Specifically, caries preventive procedures have been infrequently provided to adults in the past [2], although a recent report does suggest that dentists are now more likely to provide such procedures if they identify an adult patient as "caries active"[3].

While it is likely that there are several reasons for the dental profession's inattention to the prevention of caries in adults, lack of evidence about the effectiveness of preventive treatments in adults may be an important factor. Presumably, this lack of evidence contributes to practitioners' reluctance to provide preventive treatment to adults, and may limit purchasers' enthusiasm for coverage for such treatment. The National Institutes of Health Consensus Development Conference on Diagnosis and Management of Dental Caries Throughout Life noted that virtually all of the dental profession's knowledge concerning the effectiveness of caries preventive interventions had come from trials in children and adolescents [4]. The Conference recommended additional caries trials in adults.

In response to that recommendation we designed a randomized clinical trial, the Xylitol for Adult Caries Trial (X-ACT), to test the hypothesis that use of xylitol lozenges will reduce dental caries incidence in caries-active adults. At the time that the trial was designed, three reviews of the effectiveness of xylitol had appeared [5-7]. Although each review found evidence for a xylitol preventive effect, two reviews indicated that the available evidence was not strong enough to permit a firm conclusion of therapeutic effectiveness. All of the reviews indicated that the existing evidence needed to be supplemented by well-designed trials. Because xylitol is already approved as an over-the-counter sweetener, the intervention could be delivered outside the context of a dental office, thus making wide dissemination and implementation feasible. In addition, delivery through candy, gum, or lozenges (mints) would be likely to promote adherence to the preventive regimen. This paper describes the X-ACT protocol.

## Methods/Design

X-ACT is a three-year, multi-center, placebo-controlled, double-blind, randomized clinical trial sponsored by the National Institute of Dental and Craniofacial Research (NIDCR) that tests the effects on caries progression of daily use of xylitol lozenges versus placebo lozenges. The trial takes place in three clinical centers, which are located in the dental schools of the University of North Carolina-Chapel Hill, the University of Texas Health Sciences Center-San Antonio, and the University of Alabama-Birmingham. The Data Coordinating Center (DCC) is at the Kaiser Permanente Center for Health Research-Portland, Oregon. A Data and Safety Monitoring Board appointed by NIDCR provides oversight. The study was approved by the Institutional Review Boards at each site and all participants provided written informed consent. An overview of participant flow through the study is shown in Figure 1. Key features are a run-in period before randomization and regular contact of clinical staff with participants throughout the intervention period.

**Figure 1 F1:**
[figure not shown]
**Trial Design and Participant Contacts**.

### Study Population

Principal inclusion criteria were age 21-80 and the presence of at least one coronal or root surface cavitated caries lesion (either present at screening or documented in the dental record within the past 12 months). The caries criterion was designed to include participants who were at risk of forming new lesions. Similarly, to ensure an adequate quantity of surfaces at risk, participants were required to have a minimum of 12 teeth with exposed coronal or root surfaces. In addition, participants had to be able to read and comprehend study materials in English, and be able to give informed consent. Exclusion criteria consisted of having more than 10 teeth with caries lesions, having Type IV periodontitis, receiving long-term antibiotic therapy, needing antibiotic prophylaxis prior to dental treatment, having history of head and neck radiation therapy, a history of adverse reaction to either placebo or intervention agent, a serious illness that would interfere with participation, plans to leave the area within the next three years, no telephone, a member of the household already enrolled in the trial, or investigator option.

### Study Treatments

The intervention consisted of consumption of five lozenges daily. We chose lozenges as the delivery method on the basis of a report that lozenges were strongly preferred to gum in a sample of veterans [8] and our own perception that gum would be objectionable to some proportion of potential participants.

Each active lozenge contained 1.0 g of xylitol as a sweetening agent. The placebo lozenge was identical in size and color to the active lozenge but was sweetened with sucralose, which lacks any plausible biologic anti-caries properties. Both the active and placebo lozenges were peppermint flavored. The lozenge used for the run-in period was also sweetened with sucralose, but was spearmint flavored to avoid inadvertent unblinding of participants.

The available literature suggests, but does not demonstrate conclusively, a possible threshold of caries prevention effectiveness around 3 exposures each day with a total daily intake of 3-4 g [9]. Because we were unable to identify a manufacturer capable of compounding both active lozenges containing more than 1 g of xylitol and indistinguishable placebo lozenges, our choice of a 5 lozenge/day regimen represents a compromise between increased assurance of achieving a therapeutic dose and practicality.

Since xylitol has the capacity to act as a laxative in some individuals, participants were asked to gradually increase the number of lozenges they took each day from 1 to 5 during the first 10 days. This "ramping up" was done both during the run-in period and at the initiation of the intervention post randomization.

Lozenges were supplied to participants in containers of 75, with the participant's ID number permanently marked on the container. Seven containers constituted a 3-month supply with some extra lozenges. Participants also received a pocket container capable of holding a day's supply of five lozenges. The active and placebo lozenges were prepared in separate manufacturing runs, and samples of each run were assayed to confirm the xylitol content. The lozenge used during the run-in period was also prepared in a separate run, but was not assayed.

### Study Schedule

Figure 1 summarizes the trial flow from a participant's perspective. The study requires a participant to visit the clinic a minimum of 5 times. Screening was followed as soon as possible by an enrollment visit. The enrollment visit is followed by a placebo run-in period. Adherent, eligible enrollees were randomized at the baseline visit. Participants are then scheduled to return at 12 months, 24 months and 36 months for caries examinations, with quarterly telephone contacts between examination visits. Before the 24-month visits began, the final examination schedule was shifted to 33 months, to adjust for slower than expected completion of enrollment.

### Recruitment, Run-in and Enrollment

Recruitment of potential study participants began in April 2007, and ended in September 2008. Although the primary pool of potential study participants was dental school patients, low yields prompted two sites to expand recruitment efforts to the general public via solicitations at public dental clinics and mass media advertising. All enrollment visits were preceded by a brief conversation by telephone or in person during which eligibility and interest were assessed. Where possible, additional initial screening was accomplished by review of electronic or paper clinical records. All potential study participants attended an enrollment visit where eligibility was verified, the study was described, and requirements of participation were reviewed. Those individuals who indicated a willingness to enroll participated in a four-week run-in period [10] to help identify potential participants who were unable or unwilling to adhere to the study regimen. A call midway through the run-in period was used for data collection (adherence, side effects) and encouragement. Ultimately, 27% of those who entered the run-in period did not continue to randomization [11]. Enrollees received no financial incentives for participation in the run-in period. Financial incentives, in the form of cash payments and travel expense reimbursements, were available for enrollees who continued to the full trial.

### Randomization and Treatment Contacts

Those enrollees who completed the run-in period with adequate self-reported adherence (consumption of more than half of lozenges scheduled during the run-in period) and who indicated a willingness to participate in the full trial attended a baseline visit wherein eligibility criteria were confirmed, and a caries examination was performed. Eligible enrollees were randomized to either the active or placebo arm, additional information was collected, and the initial supply of lozenges was dispensed. Randomization was carried out using a web-based randomization application process. Allocation assignments were stratified by site and age group (≥ 50, < 50 yrs.) in permuted blocks of varying sizes within each stratum. Staff and participants were blinded to treatment assignment. A total of 691 participants were randomized, 92% of the goal of 750.

In the periods between the visits for caries examinations, participants are contacted by telephone on a quarterly basis to assess adherence, side effects, receipt of preventive dental care; to screen for possible serious adverse events; and to arrange for re-supply of lozenges. Participants are asked how many unopened bottles they have on hand, and sufficient bottles for the next three months are dispensed from the participant's master supply at the clinical site and are delivered by courier.

### Caries Examination

Caries are diagnosed visually by calibrated examiners using a CPITN-E probe, a non-magnifying plane mirror; and standard dental operating light and chair. Loupes are used at the discretion of the examiner, but consistently within each examiner. Tooth surfaces are dried for five seconds with an air/water syringe.

The X-ACT examiners use the nomenclature of Pitts and Fyffe [12] to classify the status of each tooth surface; however, the descriptors in X-ACT are a modification of the 2-digit numeric codes in the International Caries Detection and Assessment System II (ICDAS II) [13,14]. ICDAS II has established objective clinical signs that are associated with severity levels of dental caries, verified histologically. The X-ACT taxonomy does not make a number of distinctions that are in the ICDAS II taxonomy. Instead, we have collapsed codes as follows:

• First digit codes: 0 is signified by S(sound); 1, 2 are collapsed into P (pits and fissures sealed surface); 3, 4, 7, 8 are collapsed into F(filled); and 5, 6 are collapsed into C(crowned);

• Second digit codes: 0 is signified by S; 1, 2 are collapsed into a single D_1 _code (uncavitated lesion); 3, 4 are collapsed into a single D_2 _code (cavitated lesion penetrating the enamel); and 5, 6 were collapsed into a single D_3 _code (cavitated lesion penetrating into the dentin).

• Codes 97, 98 were collapsed into M (missing); 96, 99 into Y (unscorable or invisible surface)

For purposes of scoring our outcome measures, calls distinguished by P as the first character are collapsed into the most similar caries status category (see Table 1, e.g., PD_2 _with D_2_), since transition to or from a surface with pits & fissure sealant (P) does not indicate a change in caries status. Calls that signify the need for surgical intervention are treated identically, so the D_2 _and D_3 _calls are collapsed into one category. For our primary outcome, calls that do not require surgical intervention (S, D_1_) are collapsed into one category. Finally, in contrast to ICDAS II, examiners make only one diagnostic judgment per tooth surface. Each central, lateral, and canine tooth is deemed to have five coronal (including the incisal) surfaces and four root surfaces.

**Table 1 T1:** Combined D_2_FS increment: Scoring weight of changes in tooth surface for primary outcome variable

		**T**_**1**_**: Second call**							
**T_0_: First call**		**S [P D**_**1 **_**PD**_**1**_**]**	**D**_**2 **_**[D**_**3 **_**PD**_**2 **_**PD**_**3**_**]**	**F [FD**_**1**_**]**	**FD**_**2 **_**[FD**_**3**_**]**	**C [CD**_**1**_**]**	**CD**_**2 **_**[CD**_**3**_**]**	**Y**	**M**
	
	**S [P D_1 _PD_1_]**	0	1	1	1	0	0	0	0
	
	**D_2 _[D_3 _PD_2 _PD_3_]**	**-1**	0	0	0	0	0	0	0
	
	**F [FD_1_]**	**-1**	**0**	0	1	0	0	0	0
	
	**FD_2 _[FD_3_]**	**-1**	**-1**	0	0	0	0	0	0
	
	**C [CD_1_]**	**-1**	**0**	0	1	0	1	0	0
	
	**CD_2 _[CD_3_]**	**-1**	**-1**	**-1**	0	0	0	0	0
	
	**Y**	0	0	0	0	0	0	0	0
	
	**M**	0	0	0	0	0	0	0	0

S = sound

P = pit and fissure sealant

D_1 _= non-cavitated caries lesion

D_2 _= cavitated enamel caries lesion

D_3 _= caries lesion penetrating into dentin

F = filled

C = crowned

A primary examiner at each clinical center is scheduled to complete virtually all examinations. A back-up examiner can perform examinations in the event that the primary examiner is unavailable. A recorder is present for all caries examinations. Primary and back-up examiners and recorders from all three clinical centers participated in a four-day calibration session with a gold standard examiner and were certified by the DCC prior to the first baseline examinations. They also participate in refresher and reliability measurement sessions prior to the 12-, 24-, and 33-month examinations.

### Study Outcomes

#### Primary Outcome Variable

The primary study outcome is the cumulative D_2 _or Filled Surface (D_2 _FS) increment (root and coronal surfaces combined) cumulated from baseline through the three follow-up examinations. Use of the cumulative, combined D_2 _FS increment measure allows comparison with existing literature and increases confidence that any effect detected represents the prevention cavitation, which has substantial clinical implications for individuals who experience it.

The D_2 _FS increment is computed as the weighted sum, across tooth surfaces, of changes in surface status associated with 64 pre-defined transitions in tooth-surface integrity (Table 1). Our weighting scheme assigned a range of -1, 0, or +1, with transitions to a worse status receiving positive weights and transitions (reversals) to a better status receiving negative weights. No reversals are considered valid for the D_2_FS increment. A transition that reflects no change (e.g., F to F), a change from D_2 _to treated status (F or C), or to or from an unscorable status (Y or M) is scored 0 and hence effectively excluded from analysis. A transition from sound (S) to crowned (C) is given a score of 0 to minimize the influence of non-caries-related treatment on increment counts. Transition from S to CD_2 _is considered implausible given annual examinations. After completion of bootstrapping analyses of a caries increment dataset from another study, we concluded that the optimal way to handle unlikely or implausible transitions is to ignore them (i.e., assign a weight of zero). Hence for our primary analysis the bolded cells in Table 1 will be ignored, although they will be included in an outcome in planned secondary analyses.

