#### Secondary Outcome Variable

The cumulative combined D_12_FS increment (Table 2) is a variant of the primary outcome measure that adds transitions to and from non-cavitated caries (i.e., D_1_, PD_1_, FD_1_, CD_1_). This measure is constructed by scoring transitions toward worsening oral health as positive, biologically plausible "reversals" (i.e., remineralization indicated by transition from D_1 _to S) as negative, and no change or implausible/impossible as zero, and then summing over all surfaces examined. Thus, this measure can take negative values. A maximum weight of 2 is assigned to transitions observed between a pair of consecutive examinations that could theoretically be observed as intermediate steps (each contributing an increment) over two to three years of follow-up, so that the cumulative increment could not be greater than any single change. For example, an increment from S to D_2 _is given greater weight on the assumption that it should add the same increment to the cumulative score as two transitions (S to D_1_, then D_1 _to D_2_).

**Table 2 T2:** Combined D_12_FS increment: Scoring weight of transitions in tooth surface for secondary outcome variable.

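### Two scoring cells contradict the plan's own rules (F→CD2 in Table 1, D2→FD1 in Table 2), and the sentence limiting cumulative scores is too broad

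*Protocol article*

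**What the plan says.** Under Primary Outcome Variable, the protocol article defines the D2FS increment as a weighted sum over "changes in surface status associated with 64 pre-defined transitions in tooth-surface integrity (Table 1"), "with transitions to a worse status receiving positive weights and transitions (reversals) to a better status receiving negative weights". It then lists what scores zero:

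- no change;
- "a change from D_2 _to treated status (F or C), or to or from an unscorable status (Y or M) is scored 0";
- "A transition from sound (S) to crowned (C) is given a score of 0";
- S→CD2, because "Transition from S to CD_2 _is considered implausible given annual examinations";
- implausible transitions marked in bold: "for our primary analysis the bolded cells in Table 1 will be ignored".

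In Table 1 the filled row reads "F [FD_1_] -1 0 0 1 0 0 0 0", in the column order S, D2, F, FD2, C, CD2, Y, M. Only the first two entries (to S and to D2) are bolded.

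Under Secondary Outcome Variable, the D12FS increment is described as the primary measure with transitions involving non-cavitated lesions added. Single-interval jumps can weigh up to 2, "so that the cumulative increment could not be greater than any single change". The example given is S→D2, which is to count the same as S→D1 followed by D1→D2.

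**The concern.** The two matrices are the outcome definitions, so a wrong cell is a wrong count for every surface that makes that transition. F→CD2 is a move from a surface without cavitation to one with it. That is the event the primary outcome exists to count, yet it earns nothing. D2→FD1 earns a point in the secondary outcome although the more severe end state, D2→FD2, earns none. The limiting sentence describes a property that the printed weights lack, so a programmer could reasonably either add a ceiling or leave it out and obtain different secondary outcomes. If these questions are settled after the data are unblinded, the outcome definition becomes post hoc.

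**Working it through.** **Inputs.** Both matrices as printed, with bolded cells scored 0. Table 1 has 8 × 8 = 64 cells, as the text states. The worked example also reproduces in Table 2: S→D1 (1) + D1→D2 (1) = 2 = S→D2.

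**Step 1: Table 1, every move from non-cavitated to cavitated.** There are 3 × 3 = 9 such cells.

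| From | to D2 | to FD2 | to CD2 |
|---|---|---|---|
| S | 1 | 1 | 0 (named implausible) |
| F | 0 (bolded) | 1 | **0 (no stated reason)** |
| C | 0 (bolded) | 1 | 1 |

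Five cells score 1, two are bolded zeros, one is a named exception, and one (F→CD2) is unexplained.

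Supporting check by route: F→FD2→CD2 = 1 + 0 = 1 and F→C→CD2 = 0 + 1 = 1, against 0 directly. This is support only, because some other Table 1 paths also differ from their direct weight.

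**Step 2: Table 1 against Table 2.** There are 6 × 6 = 36 cells among S, D2, F, FD2, C and CD2, none of which involves a non-cavitated lesion. If Table 2 merely adds non-cavitated transitions, these cells should agree on whether an event is counted. F→CD2 is the only one that is positive in one table (2 in Table 2) and zero in the other (0 in Table 1). Table 1 also pools FD1 with F, and Table 2 scores FD1→CD2 as 1.

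**Step 3: the D2 row of Table 2.** Printed: F 0, FD1 1, FD2 0, C 0, CD1 0, CD2 0. Three possible logics were tried:

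- *A treated cavity adds nothing.* All cells should be 0; FD1 = 1 does not fit.
- *Restoration, then a new lesion, added up.* D2→F→FD1 = 0 + 1 = 1 fits. D2→F→FD2 = 0 + 2 = 2 and D2→C→CD1 = 0 + 1 = 1 do not, since both are printed as 0.
- *FD2 means the same cavity persists, FD1 means a new lesion.* CD1 should then be 1 as well; it is printed as 0.

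**Step 4: the limiting sentence (Table 2).** Among S, D1 and D2 alone, each non-bolded weight is the difference between levels 0, 1 and 2, so path sums equal the direct weight. Once a restoration enters the path:

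- S→F→FD2 = 2 + 2 = 4, direct 2
- S→D2→F→FD2 = 2 + 0 + 2 = 4, direct 2
- D2→F→FD2 = 0 + 2 = 2, direct 0
- S→D1→D2→FD1 = 1 + 1 + 1 = 3, direct 2 (caused by the D2→FD1 cell)
- largest over three intervals from S to FD2: S→FD1→C→FD2 = 2 + 1 + 2 = 5, direct 2

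The sums of 4 and 5 fail on either reading of the sentence: as a limit at the direct weight between the same end points, or as a limit at the maximum single weight of 2.

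**Step 5: effect of the D2→FD1 correction.** With D2→FD1 = 0, S→D1→D2→FD1 = 1 + 1 + 0 = 2, equal to the direct weight. Paths with recurrence after restoration still exceed it, so the sentence itself must change.

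**The case against.** *F→CD2 may be meant as implausible.* It needs a crown to be placed and then to cavitate within one interval, much like S→CD2. The absence of bold type proves little, since S→CD2 is an unbolded zero too. This is fair, and zero could be a defensible choice. It does not reconcile the tables, however: the text names only S→CD2, and Table 2 scores S→CD2 as 0 but F→CD2 as 2.

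*D2→FD1 may count a new lesion after treatment.* An increment need not rank end states. That explains this cell but not its neighbours, as Step 3 shows.

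*The sentence may concern only skipped intermediate steps.* Recurrence around a restoration is arguably a second event. This largely stands: no weight outside the D2→FD1 cell is shown to be wrong by the limit failing. The sentence is too broad as written.

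*Sensitivity analyses are planned.* The Discussion promises variations on the secondary weighting matrix. That lowers the consequence of the secondary points, but it neither corrects the main definition nor touches the primary cell.

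*A per-surface ceiling of 2 might seem the natural remedy.* It is not. Table 1 counts S→F→FD2 as 1 + 1 = 2 events, and a ceiling would reduce the corresponding D12FS score from 4 to 2, discarding a recurrent cavitation that the primary outcome keeps.

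**Conclusion.** The contradictions stand: one cell in the primary outcome, one cell in the secondary, and one over-broad sentence about the secondary. Each F→CD2 surface loses one event from the primary count. Each D2→FD1 surface gains one secondary point that the rest of its row does not support.

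The documents give no transition frequencies. On the assumptions that F→CD2 is uncommon and that both blinded arms are scored with the same weights, the effect on the primary comparison is probably small and non-directional.

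Three stronger inferences are not supported:

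- A reader might set the path differences of 2 or more points against the planned mean increment of 3.7. That figure is on the D2FS scale, from studies that did not record D1 lesions. No D12FS mean is given, so the ratio has no meaning.
- A reader might infer that the primary result is biased towards one arm. Nothing in the documents shows this.
- A reader might treat lower scores after a missed examination as a defect of these tables. That is common to increments observed at intervals and is not specific to this plan.

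**What to change.** Before unblinding:

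1. Set F→CD2 in Table 1 to 1. If the investigators judge it implausible, say so in the text and score it 0 in both tables, deciding FD1→CD2 in Table 2 at the same time because Table 1 pools FD1 with F.
2. Set D2→FD1 in Table 2 to 0, to match the rest of its row.
3. Limit the sentence about cumulative scores to forward progression of an unrestored surface (S→D1→D2), and state that a lesion recurring after restoration counts as a further event. Do not add a per-surface ceiling.

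The cost is two cells (or, if F→CD2 is declared implausible, a line of justification and the matching Table 2 entries), one sentence and the corresponding scoring code. No new data are needed.

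### In the planned secondary D2FS increment that includes the bolded Table 1 cells, a crown called sound at one follow-up examination scores -1 per surface although nothing changed, because the opposite step scores 0

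*Protocol article*

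**What the plan says.** All references are to the protocol article, Study Outcomes, Primary Outcome Variable and Table 1.

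- The D2FS increment sums weights over tooth surfaces, "associated with 64 pre-defined transitions in tooth-surface integrity (Table 1", and is "cumulated from baseline through the three follow-up examinations".
- The sign rule has worsening positive and "transitions (reversals) to a better status receiving negative weights". The text adds that "No reversals are considered valid for the D_2_FS increment".
- Crowns get separate treatment: "A transition from sound (S) to crowned (C) is given a score of 0". The reason given is to keep crowns placed for reasons other than caries from swaying the count. "Transition from S to CD_2 _is considered implausible given annual examinations", and Table 1 scores that step 0 as well.
- The Table 1 row for a surface first called crowned reads "C [CD_1_] -1 0 0 1 0 1 0 0". Its first entry, C→S, is a bolded -1.
- In the primary analysis the bolded cells count as zero, but "the bolded cells in Table 1 will be ignored, although they will be included in an outcome in planned secondary analyses". Table 1 gives the only weights shown for them.

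**The concern.** A set of transition weights that subtracts reversals behaves sensibly under examiner error if the negative weight removes something that was, or would have been, added. A filling called sound once and then called filled again loses 1 and regains 1. A crown called sound once loses 1 and regains nothing, because S→C is 0. The surface ends with a negative score although it never contributed a positive one.

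This sits badly with the article's own reasoning. S→C is zero so that crowning does not drive the count, and no reversal is accepted as real for this outcome. On that logic every C→S call is a recording error, yet it still lowers the increment. At stake is how the secondary result is read beside the primary one. Part of any gap between them would come from the scoring, and would grow with the number of crowned surfaces a participant has.

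**Working it through.** **Inputs.** Table 1, read as an 8 × 8 matrix over S, D2, F, FD2, C, CD2, Y and M. This gives 8 × 8 = 64 cells, which matches the stated number of transitions. Ten cells are bolded: eight carry -1 and two (F→D2, C→D2) carry 0.

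**Step 1: each bolded -1 against its opposite step.**

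| Bolded cell | Weight | Opposite step | Weight | Round trip |
|---|---|---|---|---|
| D2→S | -1 | S→D2 | +1 | 0 |
| F→S | -1 | S→F | +1 | 0 |
| FD2→S | -1 | S→FD2 | +1 | 0 |
| C→S | -1 | S→C | 0 | -1 |
| CD2→S | -1 | S→CD2 | 0 | -1 |
| FD2→D2 | -1 | D2→FD2 | 0 | -1 |
| CD2→D2 | -1 | D2→CD2 | 0 | -1 |
| CD2→F | -1 | F→CD2 | 0 | -1 |

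Three round trips cancel and five do not.

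**Step 2: paths over baseline and three follow-up examinations, bolded cells included.**

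- C-S-C-C: -1 + 0 + 0 = -1
- C-C-S-C: 0 - 1 + 0 = -1
- C-C-C-S: 0 + 0 - 1 = -1
- S-C-S-S: 0 - 1 + 0 = -1
- S-C-C-C (crown missed only at baseline): 0
- F-S-F-F: -1 + 1 + 0 = 0

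A filling called sound only at the last examination (F-F-F-S) also scores -1, but a filling missed only at baseline (S-F-F-F) scores +1, so the two errors balance on average. For a crown the baseline error scores 0, so nothing balances the -1.

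**Step 3: size.** Let e be the chance that a crowned surface is called sound at any one examination, independently between examinations. In each of the three intervals, C→S is recorded with probability (1 - e)e. The expected shift per crowned surface is -3e(1 - e). For a filling, the matching +1 and -1 terms sum to zero.

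The article gives neither e nor the number K of crowned surfaces, so both are assumed:

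- K = 5, e = 0.001: 5 × 3 × 0.001 × 0.999 = 0.015
- K = 10, e = 0.01: 10 × 3 × 0.01 × 0.99 = 0.297
- K = 20, e = 0.01: 20 × 3 × 0.01 × 0.99 = 0.594

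The comparison figure is the three-year total increment of 3.7 in the Sample Size section. With the planned 20% reduction the active mean is 0.8 × 3.7 = 2.96. If both arms shift by the same d, the ratio becomes (2.96 - d)/(3.7 - d):

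- d = 0.015: 2.945/3.685 = 0.799
- d = 0.297: 2.663/3.403 = 0.783
- d = 0.594: 2.366/3.106 = 0.762

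With no true effect both means shift alike and the ratio stays at 1.

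**Step 4: the three recurrent-decay cells.** When the decay was present at baseline, FD2-D2-FD2-FD2, CD2-D2-CD2-CD2 and CD2-F-CD2-CD2 each score -1. When it arose during follow-up, the -1 meets an earlier +1: F-FD2-D2-F = +1 - 1 + 0 = 0, and likewise C-CD2-D2-C and C-CD2-F-C.

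**The case against.** The strongest reply is that the weights follow two stated rules. Improvement scores negative, and S→C is zero for its own reason. The article nowhere requires opposite steps to sum to zero. A reader might infer that this secondary outcome is the declared check on ignoring reversals, and that negative weights exist to cancel examiner error. The article says neither, so the point does not rest on a broken promise. It rests on C→S working against the reason given for S→C.

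A second reply is that the -1 sometimes removes a +1 that entered by another route, as in S-F-C-S, S-D2-C-S and C-CD2-S-C, all scoring 0 as printed. It would therefore be too strong to say that all five cells always subtract caries never counted. This stands for the three recurrent-decay cells. It is weaker for C→S and CD2→S: the likeliest reading of S-F-C-S is real progression worth +1 followed by one wrong call at the end, so the -1 erases a true event.

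A third reply is that zeroing the cells trades negative residuals for positive ones. Over all 216 four-examination paths among the six scorable statuses that start and end alike, counted without regard to likelihood, the printed weights give 120 zero, 63 negative and 33 positive. With five cells at 0 the counts are 132, 15 and 69. The cost is real, but most of these paths need several changes or errors. For an unchanged surface with one wrong call, negative scores come from the -1 cells at the first or last examination and from uncancelled round trips in between. That is 8 + 8 + 5 × 2 × 2 = 36 paths as printed and 3 + 3 + 0 = 6 after the change. No +1 cell is altered, and no such path becomes positive.

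Finally, examiners are trained, calibrated and certified, staff are blinded, and a condensed article gives this outcome one clause. The full document may define it further. The Discussion plans variations on the weighting matrix, but in the context of non-cavitated lesions. All this limits the importance of the point. It does not change what the printed weights do.

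**Conclusion.** The point holds as a minor scoring fault in one secondary outcome. It is clearest for C→S and CD2→S, whose opposite steps the text itself sets aside. For FD2→D2, CD2→D2 and CD2→F the asymmetry is present but the -1 is arguable, and the sponsor should state the rule.

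A reader might infer that the primary result is biased. It is not, since these cells count as zero there. A reader might also infer that the scoring could produce a spurious treatment effect. With randomized arms and blinded staff, miscalls and crown counts should be alike in both arms, so no difference arises under the null. What remains is distortion of a ratio when an effect exists, from 0.80 to between about 0.799 and 0.762. That range rests wholly on the assumed 5 to 20 crowned surfaces, the assumed 0.1% to 1% miscall rate, independent errors and an equal shift in both arms.

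**What to change.** In the secondary outcome that includes the bolded cells, set C→S and CD2→S to 0. For FD2→D2, CD2→D2 and CD2→F, either set them to 0 as well or state why -1 is kept, for example to undo an earlier F→FD2 or C→CD2. Leave D2→S, F→S and FD2→S at -1, since their opposite steps score +1. Then C-S-C-C and S-C-S-S score 0, as F-S-F-F already does.

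The cost is two to five cells in a secondary scoring table, with no new data and no change to the primary analysis. The downside is that a few rare paths in which a miscall is followed by a different status would gain a point. C-S-F, for example, scores -1 + 1 = 0 as printed and 0 + 1 = +1 after the change.
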